| **4. Study protocol** |
| --- |
| 1. **Study population**   The study participants will be enrolled from the outpatient clinics of internal medicine department, family medicine department and Chinese medicine department of Linsen and Chinese medicine branch of Taipei City hospital.   1. **Study period**   2011/01/01 to 2012/12/31   1. **Study group**   2 groups   1. **Study duration**   16 weeks   1. **Study design**   Double blinded, randomized, and placebo-controlled trial   1. **Randomization**   The randomization sequence will be generated by a table of random numbers from the SPSS software. The allocator will have to call a central number to receive the next allocation sequence once a patient had been enrolled in the trial.   1. **Primary endpoint** 2. The percentage of change between baseline and 16 weeks in fasting triglyceride, total cholesterol, HDL, LDL. 3. Anthropometric measurements in terms of body weight, height, BMI, waist circumference, and hip circumference.   **8. Secondary endpoint**   1. The percentage of change between baseline and 16 weeks in fasting sugar, HbA1C, obesity related hormone peptides, such as leptin、adiponectin、ghrelin、fasting insulin resistance、APOB、APOA1, high sensitivity C-reactive protein (hsCRP) 2. HRQOL scores on the WHOQOL-BREF   Assessment method:  All measurements of biochemical characteristics and obesity-related hormone peptides of blood sample will be made at 0800-0900 after an overnight fasting using standardized methods. All measurements will do after an overnight fast using standardized method and will be performed in the beginning of the study and after 16 weeks of treatment. Height is measured with a wall-mounted stadiometer to the nearest 0.1 cm, weight is measured on a calibrated balance beam scale to the nearest 0.1 kg, and BMI is calculated according to the formula: BMI = body weight (BW) / height (kg/m^2^). We simultaneously collected the demographic data and fasting laboratory data such as blood sugar, creatinine, aminotransferases aspartate, aminotransferases alanine, uric acid, and plasma lipoproteins (triglyceride, cholesterol, HDL-cholesterol (HDL) and LDL-cholesterol (LDL)). Homeostasis model assessment for insulin resistance (HOMA-IR)【fasting glucose (mmol/l) × fasting insulin (UI/l)/22.5】 is used as insulin resistance measurement (25-26). All measurements will make at 0800-0900 after an overnight fast using standardized methods. A sample of whole blood was drawn and centrifuged at 4°C, and a 1-ml aliquot of serum was rapidly frozen (-80°C) for subsequent hormone analysis. The plasma adiponectin concentration will be measured by a radioimmunoassay kit (Linco Research, Inc., St. Charles, MO, USA). This kit employs the double-antibody/ polyethylene glycol technique using ^125^I-lableled adiponectin and a multispecies adiponectin rabbit antiserium. Plasma insulin levels will be measured using a commercially available radioimmunoassay (Linco Research, Inc., St. Charles, MO, USA). Plasma ghrelin levels will be measured with a commercially available radioimmunoassay (Linco Research, Inc., St. Charles, MO, USA), using ^125^I-lableled ghrelin as a tracer. The detection limitation for the assay will be 10 ng/ml.  **9. Safety evaluation**  （1）adverse event  （2）vital signs  （3）Physical examination  　 （4）laboratory evaluation including liver function and renal function  **10. Inclusion criteria**   1. Age between 20 and 65 years 2. Diagnosis of type 2 diabetes for more than one year 3. Body mass index (BMI) ≥ 18 kg/m2 and ≤ 30 kg/m2 4. Fasting triglyceride ≥ 150 mg/dl or fasting low-density-lipoprotein cholesterol (LDL) ≥ 100mg/dl 5. Willing to participate in and fill out questionnaires for this trial   **11. Exclusion criteria**   1. Serum alanine transaminase > 80 U/L 2. Serum creatinine > 1.8 mg/dl 3. Breast feeding or pregnancy 4. Heart failure, acute myocardial infarction, stroke, heavy injury 5. Any other conditions not suitable for trial as evaluated by the physician   **12. study protocol:**  All participants met the criteria will be asked to sign the informed consent form after letters explaining the purpose of the study sent to all the patients inviting their participation. Participants will be randomly allocated to receive a decaffeinated GTE EGCG (Group A) or a placebo (cellulose; Group B) for 16 weeks. Both experimental and placebo treatments were contained in the same opaque capsules, which will be administered by a blinded research assistant. Participants will be instructed to maintain an isocaloric diet and to continue their previous eating habits during the study period. Every four weeks, Participants will return to our clinics and report to the study center for adverse events and compliance assessment. Participants will be free to withdraw at any time. Throughout the study period, participants will be directed to continue taking the same dose of any prescribed hypoglycemic agents unless hypoglycemia or severe complications occurred, in which case they will be directed to reduce their dose immediately.  **13. Adverse event report**  We will assess any adverse event of the participants during the study and will discuss the necessary to drop out.  **14. Drop out/ withdraw criteria**   - 1. drug compliance < 60% or no willing to return during the study   2. pregnancy occurred during the study   3. major illness or hospitalization occurred during the study   4. the dose of antidiabetic or antihyperlipidemia medication changed during the study   5. not suitable to participant after doctor assessed during the study   6. lost of follow up or death   **15. Statistical analysis**   1. The data will be analyzed using SPSS software (version 17.0, Chicago, IL.) 2. Independent t-tests will be employed to examine the difference in anthropometrics, biochemical characteristics, obesity-related hormone peptides, and life-quality scores between EGCG group and placebo group. 3. Paired t-tests will be employed to examine the difference between before and after intervention for 16 weeks in both groups. 4. All p values will be two-tailed and α level of significance will be set at 0.05. 5. This study population will be “Intent to treat population” for analysis of therapeutic efficacy 6. The definition of ITT （Intent to treat population）is that participants take the study medication once.   **16. Preparation of samples and placebo**  Decaffeinated GTE was obtained by [name] from the Tea Research and Extension Station, Taoyuan County, Taiwan. It was extracted from dried leaves of green tea according to pre-set standard procedures. The decaffeinated GTE used in this study was standardized for several tea catechins in addition to EGCG. The placebo comprised pure microcrystalline cellulose. Capsules contained either 500 mg decaffeinated GTE extract or cellulose. This sample contains 57.12% EGCG (80.83% Total catechines.  [figure not shown]  （1）The machine was used to extract decaffeinated GTE.  [figure not shown]  （2）Placebo (B group) was made by cellulose. |

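### A participant who obeys item 12's dose-reduction instruction meets an item 14 withdrawal criterion, and nothing secures the week-16 measurement that item 15's ITT analysis needs

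*Protocol*

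**What the plan says.** All references are to the protocol, section 4.

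- **Item 12 (study protocol)** asks participants to hold their prescribed hypoglycaemic dose constant "unless hypoglycemia or severe complications occurred, in which case they will be directed to reduce their dose immediately". It does not say whether they then stay in the study.
- **Item 13 (adverse event report)** says that whether a participant needs to drop out after an adverse event will be discussed.
- **Item 14 (drop out / withdraw criteria), criterion 4**, lists "the dose of antidiabetic or antihyperlipidemia medication changed during the study". It makes no distinction by direction, by reason, or by whether the protocol directed the change.
- **Item 15 (statistical analysis)** states: "This study population will be “Intent to treat population” for analysis of therapeutic efficacy". The definition of that population "is that participants take the study medication once". Meeting an item 14 criterion later is not a ground for exclusion.
- **Item 8, assessment method,** says that measurements "will be performed in the beginning of the study and after 16 weeks of treatment". The four-weekly visits in item 12 are for adverse events and compliance.
- **Endpoints.** The primary endpoints (item 7) include "The percentage of change between baseline and 16 weeks in fasting triglyceride, total cholesterol, HDL, LDL". The glycaemic measures are secondary (item 8): "The percentage of change between baseline and 16 weeks in fasting sugar, HbA1C", with insulin resistance in the same list.

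**The concern.** A participant can do exactly what item 12 directs and, by doing so, satisfy a withdrawal criterion. The event behind the reduction, hypoglycaemia, is related to glucose, and glucose is an outcome of the trial. If EGCG lowers glucose, such reductions may be more frequent in the EGCG group. Withdrawal would then be related to outcome and uneven between arms.

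The link to item 15 makes this a statistical matter. The ITT definition keeps the participant in the efficacy population, but an outcome value exists only if the participant is measured at week 16. If withdrawal ends measurement, the participant counts as ITT and has no percentage change to enter in the t-test. The comparison is then one of completers under an ITT label.

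Criterion 4 also covers lipid-lowering drugs. Participants enter with raised triglyceride or LDL (item 10), so changes in lipid-lowering dose during 16 weeks are foreseeable. If such changes depend on lipid response, the loss falls on the primary lipid endpoints.

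**Working it through.** **Step 1: follow one participant through the items.**

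| Event | Item | Stated consequence |
|---|---|---|
| Hypoglycaemia or severe complication | 12 | Hypoglycaemic dose is reduced |
| The same event as an adverse event | 13 | Need for drop-out is discussed |
| The dose has now changed | 14, criterion 4 | Drop-out/withdrawal criterion is met |
| Study medication was taken at least once | 15 | Participant stays in the ITT efficacy population |
| Week 16 | 8 | Measurement planned; nothing said about withdrawn participants |

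Items 12 and 14 can be read in sequence: reduce, then withdraw. On that reading they do not contradict each other literally, but withdrawal still follows from an outcome-related event. Item 13 leaves open whether withdrawal is automatic or a matter of judgement.

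**Step 2: look for a figure to reproduce.** The protocol gives no sample size, SD, effect size, hypoglycaemia rate or drop-out rate. The size of any bias cannot be derived from it.

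**Step 3: check the direction only, under assumed inputs.** Let glycaemic change in SD units be N(0, 1) on placebo and N(−d, 1) on EGCG, negative being better. A share q of those below a cutoff c is withdrawn without a week-16 value. For an arm with mean μ, let a = c − μ, and let Φ and φ be the standard normal distribution function and density:

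- share withdrawn = q·Φ(a)
- mean of those kept = [μ − q·(μ·Φ(a) − φ(a))] / [1 − q·Φ(a)]

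Worked case: d = 0.5, c = −1.645 (5% of placebo below it), q = 1.

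- Placebo: a = −1.645, Φ = 0.050, φ = 0.1031. Mean kept = 0.1031 / 0.950 = 0.1086.
- EGCG: a = −1.145, Φ = 0.126, φ = 0.2072. Mean kept = [−0.5 − (−0.0631 − 0.2072)] / 0.874 = −0.2629.
- Completers' difference = 0.1086 + 0.2629 = 0.3715, against 0.50: about 26% smaller, with 5.0% and 12.6% withdrawn.

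The grid was d = 0.3 or 0.5; 2%, 5% or 10% of placebo below the cutoff; q = 0.5 or 1. Selected results, including both extremes:

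| d | Placebo below cutoff | q | Withdrawn, placebo / EGCG | Completers' difference | Shrinkage |
|---|---|---|---|---|---|
| 0.3 | 2% | 0.5 | 1.0% / 2.0% | 0.281 | 6% |
| 0.3 | 5% | 1 | 5.0% / 8.9% | 0.231 | 23% |
| 0.5 | 5% | 0.5 | 2.5% / 6.3% | 0.442 | 12% |
| 0.5 | 5% | 1 | 5.0% / 12.6% | 0.372 | 26% |
| 0.5 | 10% | 1 | 10.0% / 21.7% | 0.319 | 36% |

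If withdrawal is unrelated to response, the mean of those kept is μ in each arm, the difference is d, and there is no bias.

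**The case against.** **The items may simply run in sequence.** Item 12 is a safety instruction. A reader might infer that it treats the reduction as a permitted event after which the participant carries on, so that item 14 flatly contradicts it. The text does not say that. This objection stands: the fault is that the consequence is not settled across items 12, 13 and 14, not that two opposite consequences are stated.

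**Item 15 already keeps these participants.** A reader might infer that responders are removed from the analysis. Item 15 excludes nobody for meeting item 14, so this is not supported. The methods for handling missing values may properly be left to an SAP. What remains is the measurement itself: an SAP cannot supply a week-16 blood sample that was never drawn.

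**The size is speculative.** One could assume an SD of 20 points for percentage change in fasting glucose, a true difference of −8, and loss of everyone falling by more than 30%. The completers' difference would then be −5.7, which is 28% smaller. The arithmetic is right, but the protocol's trigger is hypoglycaemia or severe complications, not a percentage fall. The cutoff in the grid above is a stand-in with the same weakness. Hypoglycaemia can also occur on placebo, and reductions for severe complications need not mark responders. Nor would keeping these participants fully restore the assumed difference, because some would be measured on a reduced background dose. All of this stands, so the calculation shows direction only.

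**The scope of items 12 and 14 differs.** Item 12 addresses hypoglycaemic agents only, and item 14 also covers lipid-lowering drugs. A reader might call this a second contradiction. It is not: a list of withdrawal reasons may be wider than one instruction, and this entry can be seen as guarding the lipid endpoints against confounding.

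**Conclusion.** The concern holds in a limited form. Following item 12 meets item 14 criterion 4, and the protocol does not secure the week-16 value that its own ITT analysis requires.

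Bias in fasting sugar, HbA1c and HOMA-IR is conditional. It needs missing week-16 values and dose reductions related to glycaemic response. Given both, the likely direction is towards no effect. The illustrative 6% to 36% rests wholly on the assumed inputs, and the document supports no estimate. These endpoints are secondary. For the primary lipid endpoints the risk has the same form, but it depends on lipid-lowering changes following lipid response, and no size is claimed.

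This is a correction worth making because it is cheap and missing samples cannot be recovered later. The documents do not show that the primary result is compromised.

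**What to change.** 1. Reconcile items 12, 14 and 15, with item 13 in view, so that a directed dose change has one stated consequence. Which clinical rule is kept is for the investigators, and this review does not choose it.
2. Whichever rule is kept, state that week-16 measurements are still taken in consenting participants after a dose change or withdrawal, for antidiabetic and lipid-lowering drugs alike.
3. State that these participants are analysed in their randomised group under the ITT definition of item 15.
4. Tabulate dose changes by arm, with drug class, direction and reason, so that any imbalance is visible.

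The cost is a few sentences of protocol text, one table and a little more follow-up. The downside is that some week-16 values will reflect a changed background dose. The table in point 4 lets readers see how many.

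### The withdrawal rules conflict with the promised intent-to-treat analysis, because no week-16 measurement is provided for patients who are withdrawn

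*Protocol*

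**What the plan says.** All references are to section 4 of the protocol.

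- **Efficacy population (item 15).** Efficacy is to be analysed in an ITT population, defined by the condition that "participants take the study medication once". Between-group comparisons are independent t-tests.
- **Withdrawal (item 14).** The grounds include "drug compliance < 60% or no willing to return during the study", "major illness or hospitalization occurred during the study", "the dose of antidiabetic or antihyperlipidemia medication changed during the study" and "not suitable to participant after doctor assessed during the study". Pregnancy, loss to follow-up and death are also listed.
- **Dose changes (item 12).** Patients are to keep their hypoglycaemic dose unless hypoglycaemia or severe complications occur, "in which case they will be directed to reduce their dose immediately".
- **Timing of measurement (items 7, 8 and 12).** The primary lipid endpoint is the percentage change from baseline to week 16. Measurements "will be performed in the beginning of the study and after 16 weeks of treatment". At the four-weekly visits patients "report to the study center for adverse events and compliance assessment"; no efficacy measurement is planned there.

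The protocol does not describe any assessment at or after withdrawal.

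**The concern.** A patient who takes one capsule belongs to the ITT set for good. If that patient later meets an item 14 criterion and leaves before week 16, the set still includes the patient but the endpoint does not exist. A t-test on change to week 16 can then use only those who stayed: broadly, patients who took at least 60% of the capsules, were not seriously ill and had no change of dose.

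The dose-change criterion deserves most attention. Antidiabetic and lipid-lowering doses can be changed because of glucose and lipid values, and those are the secondary and primary endpoints. Item 12 directs one such change and item 14 then makes it a ground for withdrawal, so following the protocol can itself create missing data linked to outcome. The doctor's-judgement criterion adds removals with no objective rule.

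What is at stake is the randomised comparison on the primary and secondary endpoints. An analysis plan can choose how to handle missing values, but it cannot supply week-16 blood that was never drawn.

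**Working it through.** **Step 1. Follow one patient through the items.** Take a patient dosed on day 1 whose hypoglycaemic dose is reduced at week 6 because of hypoglycaemia.

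| Item | Consequence |
|---|---|
| 12 | The dose reduction is directed by the protocol |
| 14 | The dose change is a withdrawal criterion |
| 8 and 12 | Efficacy is measured at baseline and week 16 only; the visits in between cover adverse events and compliance |
| 15 | The patient is in the ITT set, having taken study medication |

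The last row needs a week-16 value that no other row provides.

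**Step 2. How large could the bias be?** The protocol gives no SD, effect size, dropout rate or sample size, so there is no stated figure to reproduce and every input here is assumed. Let Y be the LDL percentage change: placebo N(0, 20²), active N(-8, 20²). A withdrawal score is L = ρ·Y/20 + √(1 − ρ²)·e, with e standard normal. A patient is withdrawn if L exceeds c = 1.25, in either arm. This withdraws 1 − Φ(1.25) = 10.6% on placebo.

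The score has mean 0 on placebo and −0.4ρ on active, since −8/20 = −0.4. The active arm's effective cut-off is therefore 1.25 + 0.4ρ. With h(x) = φ(x)/Φ(x), the means among those who remain are

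- placebo: −20ρ·h(1.25), with h(1.25) = 0.2042
- active: −8 − 20ρ·h(1.25 + 0.4ρ)

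so the observed difference is −8 + 20ρ·[h(1.25) − h(1.25 + 0.4ρ)].

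| ρ | Active cut-off | Active withdrawn | h(active) | Observed difference | Attenuation |
|---|---|---|---|---|---|
| 0 | 1.25 | 10.6% | 0.2042 | −8.0 | 0% |
| 0.3 | 1.37 | 8.5% | 0.1706 | −8 + 6 × 0.0336 = −7.8 | 2.5% |
| 0.6 | 1.49 | 6.8% | 0.1411 | −8 + 12 × 0.0631 = −7.2 | 9.5% |
| 1 | 1.65 | 4.9% | 0.1076 | −8 + 20 × 0.0966 = −6.1 | 24% |

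The last row is the extreme case: every patient whose LDL rises by more than 25% is withdrawn, and nobody else.

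**Step 3. What if withdrawal rates differ for other reasons?** A simulation with a different set of assumptions (SD 25 points, completers only, withdrawal related to worsening) gave:

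| Withdrawn, active / placebo | Correlation | Shift when the true difference is 0 | A true −10 becomes | Type I error, 50 / 100 per arm (nominal 0.05) |
|---|---|---|---|---|
| 10% / 10% | 0.6 | about 0 | −9.9 | 0.050 / 0.054 |
| 10% / 20% | 0.3 | +1.2 | −8.9 | 0.057 / 0.061 |
| 10% / 20% | 0.6 | +2.3 | −7.7 | 0.074 / 0.099 |
| 10% / 30% | 0.6 | +4.5 | −5.5 | 0.137 / 0.228 |

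Equal withdrawal, or withdrawal unrelated to outcome, gave no material bias. With no week-16 values missing, the difference was recovered without bias.

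**The case against.** A reader might infer that the ITT analysis cannot be delivered and that a biased completer analysis is certain. The protocol does not support that. Item 14 does not say that withdrawn patients go unmeasured or are excluded from analysis, nor whether withdrawal means from the capsules or from the study. Item 15 keeps every dosed patient in the efficacy set. The handling of missing values may stand in an analysis plan that is not shown, and its absence from the protocol is no fault. These points stand, and they are why the conclusion is a risk and an unreconciled conflict.

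Further points also stand:

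- Not every criterion is tied to the endpoints; pregnancy is an example. Loss to follow-up and death would cost data under any design. The compliance criterion is weaker evidence of a link to outcome than the dose-change criterion.
- No lipid value planned in the trial before week 16 could prompt a drug change. The trigger would have to come from routine care, or from the hypoglycaemia and severe complications named in item 12. A 24% attenuation is therefore an upper-end figure for the chosen inputs.
- The larger shifts and the raised type I error need withdrawal rates that are assumed to differ between arms.
- A one-dose set is a common modified ITT. With blinded, identical capsules, patients who are never dosed are unlikely to differ by arm, so this is a minor matter of labelling.

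The conflict itself survives. Item 14 places these criteria in one list with loss to follow-up and death under a heading on dropping out, and nothing in the protocol keeps a withdrawn patient in follow-up.

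**Conclusion.** The point holds as a conflict among items 12, 14 and 15, combined with the lack of any provision for week-16 measurement after withdrawal. As written, withdrawn patients' endpoints would probably be missing, and the analysis labelled ITT risks covering completers only.

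The size of any bias is uncertain. It requires withdrawal that both differs by arm and relates to outcome. Under the assumptions of Step 2, a true difference of −8 is observed as about −7.8 to −7.2 at moderate correlations and as −6.1 at the extreme. These scenarios attenuate the effect, but the direction in the actual trial depends on which patients leave which arm, and the protocol gives nothing to settle it. Confidence is high on the conflict and low on the magnitude. The reason to act is that the loss cannot be undone after week 16 and is cheap to prevent.

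**What to change.** Reconcile items 12, 14 and 15 without changing any clinical rule:

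1. In item 14, separate stopping the capsules from leaving follow-up.
2. State that every randomised patient who has not withdrawn consent has the planned week-16 fasting blood, anthropometrics and WHOQOL-BREF, whatever the compliance or drug change.
3. In item 15, define ITT as all randomised patients, analysed in the arm assigned. If the one-dose condition is kept, call the set modified ITT.
4. Use compliance of at least 60% and unchanged concomitant dose only to define a per-protocol sensitivity set.
5. Record every change in antidiabetic or lipid-lowering medication with its date.

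The cost is protocol wording and a few additional patients at a visit that is already scheduled. The drawback is that week-16 values after a drug change include the effect of that change; the per-protocol sensitivity analysis and the dated records let readers see how much this matters.

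### Background drug changes disqualify a patient only after entry: no stable-treatment period is required before baseline, which costs precision between arms and biases the within-arm before-after tests

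*Protocol*

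**What the plan says.** **After entry.** Protocol item 14 lists as a reason for withdrawal that "the dose of antidiabetic or antihyperlipidemia medication changed during the study". Item 12 adds an instruction to participants for one of those two drug classes: "participants will be directed to continue taking the same dose of any prescribed hypoglycemic agents unless hypoglycemia or severe complications occurred". In those cases they are told to reduce the dose.

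**Before entry.** Item 10 has five inclusion criteria and item 11 five exclusion criteria. None sets a stable-dose period, a run-in or a washout. The only duration required before entry is "Diagnosis of type 2 diabetes for more than one year", which concerns the disease and not its treatment. The lipid criterion, "Fasting triglyceride ≥ 150 mg/dl or fasting low-density-lipoprotein cholesterol (LDL) ≥ 100mg/dl", carries no condition on lipid-lowering treatment. The one exclusion that could reach a recent drug change is general: "Any other conditions not suitable for trial as evaluated by the physician".

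**What is measured.** The first-listed primary endpoint (item 7) is "The percentage of change between baseline and 16 weeks in fasting triglyceride, total cholesterol, HDL, LDL". Item 8 uses the same measure for secondary endpoints, starting with "The percentage of change between baseline and 16 weeks in fasting sugar, HbA1C". Item 8 places the measurements at the start of the study and after 16 weeks only. Item 15 compares the arms by independent t-tests and compares before with after in each arm by paired t-tests.

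**The concern.** Item 14 shows that the plan already treats a change in these drugs as incompatible with its endpoints. The protection starts at entry, however, whereas a drug's effect can run on after the day on which it was started or adjusted. A clinic patient whose lipid-lowering drug was started shortly before enrolment, and whose LDL is still at or above 100 mg/dl, meets item 10. If the dose then stays the same, no rule is broken, yet the rest of the drug's effect falls between baseline and week 16. The same applies to a recent antidiabetic change and the glycaemic endpoints.

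Two things are at stake. In the between-arm comparison, a mixture of settled and unsettled patients widens the spread of the changes and lowers power. In the within-arm paired tests, a drift unrelated to the study product is read as a change over the treatment period, and those tests have no control arm to remove it.

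**Working it through.** **No figure to reproduce.** The protocol states no sample size, power, SD or expected effect. From it come only the endpoint (percentage change to 16 weeks), the two kinds of t-test and the two-sided 5% level.

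**Assumed inputs** (none is in the protocol):
- SD of LDL percentage change among settled patients: s = 15 points (range 12 to 20).
- Share of recent starters: f = 5%, 10% or 20%.
- Further fall still to come in a recent starter: m = 10, 20 or 30 points. The top value stands for a patient with nearly the whole drug effect still ahead.
- Power with settled patients only: 80%.
- For the paired test: 40 patients per arm, and no other cause of change.

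**Step 1: spread.** With the same f and m in both arms, the SD becomes s' = √(s² + f(1 − f)m²). For s = 15, f = 0.10, m = 30: √(225 + 0.09 × 900) = √306 = 17.5, so the variance is multiplied by 306/225 = 1.36.

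**Step 2: between-arm power.** At a fixed sample size, power = Φ(2.802 × s/s' − 1.96), where 2.802 = 1.960 + 0.842. For the same case: Φ(2.802 × 15/17.49 − 1.96) = Φ(0.443) = 67%.

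| Residual effect (s = 15) | f = 5% | f = 10% | f = 20% |
|---|---|---|---|
| 10 points | 79% | 78% | 77% |
| 20 points | 77% | 74% | 70% |
| 30 points | 73% | 67% | 59% |

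At 30 points, power is 69/61/51% for s = 12 and 76/72/67% for s = 20. A separate calculation, with s = 20 to 25, 40 per arm and a true effect of 0.6 SD, starts at 76.5% and ends between 76.2% and 63.3%.

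**Step 3: within-arm paired test, no treatment effect.** The mean change in each arm shifts by f × m, with standard error s'/√40. For f = 0.10, m = 30: shift 3.0, standard error 17.49/6.325 = 2.77, ratio z = 1.085. The probability of rejection is Φ(z − 1.96) + Φ(−z − 1.96) = 19.2%, against a nominal 5%.

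| Residual effect (s = 15) | f = 5% | f = 10% | f = 20% |
|---|---|---|---|
| 10 points | 5.5% | 7.0% | 12.9% |
| 20 points | 6.9% | 12.3% | 31.9% |
| 30 points | 8.9% | 19.2% | 50.6% |

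**Step 4: is chance imbalance an extra harm?** With 40 per arm, 10% recent starters and m = 30, chance differences in their number add an SD of 30 × √(2 × 0.1 × 0.9/40) = 2.0 points to the arm difference. The standard error of that difference is 15 × √(2/40) = 3.35 without recent starters and 17.49 × √(2/40) = 3.91 with them, and √(3.91² − 3.35²) = 2.0. This is the variance inflation of step 1 seen from another side, so it must not be added to the power loss.

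**The case against.** The strongest reply is that a randomised, placebo-controlled comparison already deals with this. Recent starters fall into both arms in equal expectation, and the t-test's standard error includes the extra spread. That stands. A reader might infer that the between-arm result is biased or its type I error inflated. The protocol does not support that reading: a chance imbalance in recent starters is ordinary sampling error, already counted (step 4). The reply does not reach the paired tests of item 15, which use each arm alone.

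The size may also be small. A patient some weeks into treatment has less effect to come than a new starter, and a dose change need not act like a new drug. With a 10-point residual effect the power loss is one to three percentage points. The figures also concern LDL only, one of four lipids. All this stands, so no single figure should be read as the trial's actual loss.

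The physician's discretion under item 11 may remove some of these patients. It does not mention medication, so it is not a rule and may be applied unevenly.

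A reader might also infer that lipid-lowering treatment is left free after entry, because item 12 names only hypoglycaemic agents. That goes too far: item 14 makes a change in either class a ground for withdrawal. What is missing after entry is a matching instruction.

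An unseen SAP does not answer the point, because it cannot supply an eligibility criterion.

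**Conclusion.** The gap is certain on the text; its size is not known. Treatment must be constant after entry but need not be settled at entry, so an unfinished drug effect can enter the primary lipid endpoints and the glycaemic secondary endpoints. The consequence is lost precision between arms and direct bias in the within-arm paired tests.

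On the stated assumptions, the loss runs from negligible (few recent starters, little effect to come) to about 20 percentage points of power, with about half of null paired tests rejecting (20% recent starters, 30 points). The share of recent starters and the residual effect decide where the trial falls, and the protocol gives neither. This is a worthwhile, inexpensive improvement to the design. It does not invalidate the randomised comparison.

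Items 12 and 14 also disagree. The same-dose instruction covers one drug class and the withdrawal rule two. Item 12 also directs a dose reduction in circumstances where item 14 would make that same change a withdrawal criterion.

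**What to change.** Add one criterion to item 10: lipid-lowering and antidiabetic treatment, or its absence, has been unchanged for a fixed period before the baseline draw. The sponsor should choose the period and justify it against how long the lipid and glycaemic measures take to settle. Record at screening the start date and date of last change of each such drug, so that compliance can be checked and the balance between arms described.

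Separately, reconcile items 12 and 14 so that they cover the same drug classes and agree on the status of a participant whose dose is reduced as item 12 directs. Which rule applies is a clinical matter for the sponsor and investigators.

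The cost is one criterion, a few screening fields and a wording change, with no extra visit or test. Recent starters would be deferred, which slows recruitment in proportion to their share. If they are few, both the cost and the gain are small. If they approach 20%, the gain is material, but so is the delay within the fixed 2011 to 2012 study period.
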